### Study design

A randomized, adaptive, PbO-controlled, multiarm, multistage trial conducted in 3 continuous stages (ClinicalTrials.gov Identifier: NCT04468087); version 4.0 of Protocol 10/07/2020. The first two stages are Phase II studies, and the third is a Phase III study, as shown in figure 1.

**Figure 1 f1:**
[figure not shown]
Study flowchart. ATV - atazanavir; SOF - sofosbuvir; DCV - daclatasvir.

## METHODS

### Study settings

The study will be conducted in approximately 60 Brazilian hospitals.

### Eligibility criteria

The inclusion and exclusion criteria are described in table 2. Procedures for the initial diagnosis of COVID-19, collection of biological material, viral identification, genetic sequencing and viral isolation in culture are explained in Supplementary material 1.

**Table 2 t2:** Inclusion and exclusion criteria

Inclusion criteria	Exclusion criteria
1. Adults (≥ 18 years) hospitalized with COVID-19 with one of the following conditions: - Positive RT-PCR test for SARS-CoV-2 OR - Typical clinical history AND chest CT with typical findings, pending the results of the RT-PCR test for SARS-CoV-2 2. Time between symptom onset and inclusion ≤ 9 days 3. SpO2 ≤ 94% in room air or need for supplemental oxygen to maintain an SpO2 > 94% 4. The patient consents to participate in the study and is willing to comply with all study procedures, including the collection of virology samples	Presence of any of the following conditions: - Patients requiring invasive mechanical ventilation - ALT or AST level > 5 times the upper limit of normal - Total bilirubin level > 2mg/dL - Platelet count < 50,000 cells/L - Total neutrophil count < 750 cells/L - Renal failure (eGFR < 30mL/min/1.73m^^2^^, using the MDRD or CKD-EPI method); and predefined renal failure Stage 3 according to the AKIN^(9)^ classification with a serum creatinine level > 4mg/dL or patient already on renal replacement therapy - History of liver disease with moderate to severe impairment (liver cirrhosis with - Child Pugh B and C classification) previously known* - Decompensated congestive heart failure* - Pregnant or breastfeeding patients - Known allergy or hypersensitivity to any study drug - Carrier of hepatitis C (positive HCV RNA), active hepatitis B (positive surface antigen in the past), or HIV (ELISA and confirmatory Western blot in the past) - Patients currently using nucleoside or nucleotide analog drugs for any indication - Corrected QT interval > 480 on the electrocardiogram - Heart rate < 55 bpm - Patients using or who recently used (< 90 days) amiodarone - Women of childbearing potential* or men with a partner of childbearing potential who do NOT agree to use two contraceptive methods (including barrier method) for 100 days

RT-PCR - real time polymerase chain reaction; CT - computed tomography; SpO2 - oxygen saturation; ALT - alanine aminotransferase; AST - aspartate aminotransferase; eGFR - estimated glomerular filtration rate; MDRD - Modification of Diet in Renal Disease; CKD-EPI - Chronic Kidney Disease Epidemiology Collaboration; AKIN - Acute Kidney Injury Network; HCV - hepatitis C virus; ELISA - enzyme-linked immunosorbent assay.

* Defined in Supplementary material 1.

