## INTRODUCTION

### Background and rationale

Coronavirus disease 2019 (COVID-19) reached a pandemic status, and several approaches have been suggested to control severe acute respiratory syndrome coronavirus 2 (SARS-CoV-2) replication in patients with moderate to severe cases. One of these strategies includes the repurposing of antiviral drugs used to treat severe acute respiratory syndrome coronavirus 1 (SARS-CoV-1) and Middle East respiratory syndrome coronavirus (MERS-CoV), including antiretroviral agents.^(1)^ Drugs such as remdesivir, lopinavir and ritonavir, darunavir and cobicistat, umifenovir and oseltamivir potentially exert therapeutic effects against COVID-19.^(2)^ However, among these repurposed drugs, only remdesivir showed clinical benefits for COVID-19 treatment.^(3)^

Other specific and nonspecific antivirals have been proposed to treat the disease. Some are based on the results from in vitro and clinical studies conducted with a small sample size in specific populations. Atazanavir (ATV) blocked the major protease activity of SARS-CoV-2 in a protease-free cell assay;^(4)^ sofosbuvir (SOF) showed EC_50_ values against SARS-CoV-2 replication of 6.2 and 9.5µM in HuH7 (hepatoma) and Calu-3 (type II pneumocytes) cells, respectively;^(5)^ and daclatasvir (DCV) consistently inhibited the production of SARS-CoV-2 infectious particles in Vero cells, the HuH-7-cell line and Calu-3 cells, preventing the induction of interleukin (IL) 6 and tumor necrosis factor alpha (TNF-α) production.^(5)^ Available clinical studies are synthesized in recent meta-analysis, SOF/DCV may reduce the mortality rate and need for intensive care unit (ICU)/invasive mechanical ventilation (IMV) in patients with COVID-19 while increasing the chance for clinical recovery with a low to moderate quality of evidence.^(6)^ However, no studies investigating DCV or ATV alone have been published.

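### Table 2 gives the platelet and neutrophil exclusion limits per litre, a unit in which they exclude essentially nobody; probably a unit slip to be reconciled

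*Protocol article*

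**What the plan says.** The exclusion column of Table 2 opens with "Presence of any of the following conditions", so each entry excludes a patient on its own. Two adjacent entries are blood counts: "Platelet count < 50,000 cells/L - Total neutrophil count < 750 cells/L". Both use cells per litre.

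No other part of the article gives a platelet or neutrophil limit. The note under the table expands abbreviations and explains the asterisk ("Defined in Supplementary material 1"). It does not redefine the unit, and neither blood-count entry carries an asterisk. Bilirubin, creatinine and eGFR, in the same list, are given in usable units.

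**The concern.** An eligibility limit works only if its numeral and unit together describe a value that patients can have. Blood counts per litre run to about 10^11 for platelets and 10^9 for neutrophils, so limits of 50,000 and 750 per litre lie far outside the range seen in practice. These are the only two exclusions based on blood counts. Applied as printed, they would admit patients with severe thrombocytopenia or neutropenia, and enrolling such a patient would not count as a breach of the eligibility criteria, although the section on protocol violations and deviations asks for major breaches of this kind to be reported.

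The article also says, in its Discussion, that its content agrees with the protocol approved by the ethics committees and the regulator. A reader therefore cannot simply assume that the unit is wrong in the article alone.

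**Working it through.** The check is a unit conversion. The plan derives no figure here, so there is none to reproduce.

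**Inputs from Table 2:** platelets below 50,000 cells/L; neutrophils below 750 cells/L. **Conversion:** 1 L = 1,000,000 µL.

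**1. The limits as printed, in units that laboratories commonly report**

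- Platelets: 50,000 / 1,000,000 = 0.05 per µL; 50,000 / 10^9 = 0.00005 x 10^9/L.
- Neutrophils: 750 / 1,000,000 = 0.00075 per µL; 750 / 10^9 = 0.00000075 x 10^9/L.

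**2. Low counts chosen for illustration (not from the documents)**

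- Platelets of 20 x 10^9/L: 20,000,000,000 / 50,000 = 400,000 times the limit. Not excluded.
- Neutrophils of 0.3 x 10^9/L: 300,000,000 / 750 = 400,000 times the limit. Not excluded.

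**3. Comparison with usual adult values.** The article gives no reference ranges. Assume 150 to 400 x 10^9/L for platelets and 1.5 to 8 x 10^9/L for neutrophils.

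- Platelets: 150 x 10^9 / 50,000 = 3 million; 400 x 10^9 / 50,000 = 8 million.
- Neutrophils: 1.5 x 10^9 / 750 = 2 million; 8 x 10^9 / 750 = about 10.7 million.

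The printed limits are smaller than usual values by these factors.

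**4. The limits as whole-body totals,** assuming 4 to 6 L of blood

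- Platelets: 4 x 50,000 = 200,000 to 6 x 50,000 = 300,000 cells.
- Neutrophils: 4 x 750 = 3,000 to 6 x 750 = 4,500 cells.

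A routine blood count cannot resolve numbers this small.

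**5. The same numerals read per microlitre**

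- Platelets: 50,000 x 1,000,000 / 10^9 = 50 x 10^9/L.
- Neutrophils: 750 x 1,000,000 / 10^9 = 0.75 x 10^9/L.

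The two readings differ by a factor of 1,000,000. Step 5 shows the scale of the discrepancy only; it does not endorse any limit.

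**The case against.** **The slip is too obvious to matter.** A factor of a million is hard to overlook, and site staff comparing a routine count with the table would probably see what was meant. This bears on the likely impact, and it stands: a reader might infer that the same patient would be eligible at one of the roughly 60 hospitals and ineligible at another, but nothing in the article shows that sites differed. It does not make the printed criteria right.

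**Sites worked from the full protocol.** This also stands. The article was published late, by its own account, and 256 patients had been randomised by July 2021. It does not show which unit the protocol or the eligibility form uses. The Discussion's general assurance of consistency settles the matter in neither direction.

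**A micro sign may have been lost in the table.** This cannot be ruled out: a dropped sign would explain both entries at once, and the superscript in the eGFR unit of the same table is garbled. Against it, the sign survives in Background and rationale ("EC_50_ values against SARS-CoV-2 replication of 6.2 and 9.5µM"), and the ≤ and ≥ signs survive in Table 2. The text at hand states litres twice.

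**Further consequences that a reader might infer, but that the article does not support:**

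- That no living patient could meet the criteria. A neutrophil count reported as zero is below 750 per litre, so that criterion would still catch such a patient.
- That cytopenias already present at entry would inflate the adverse-event results. Table 1 restricts the graded adverse-event outcome to events that were absent at entry, and the Grade 4 laboratory criterion for stopping study drug applies only to abnormalities attributed to it.
- That an electronic eligibility check needs reprogramming. The article describes a web-based randomisation system and a data-capture system, but no automated check of laboratory values.

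**Conclusion.** The point holds as a minor correction to two operative eligibility thresholds. In the printed unit, both blood-count exclusions have no practical effect, and nothing in the article supplies a workable unit. A slip in the unit is the probable cause.

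The conclusion that the limits exclude essentially nobody rests on the unit conversion and on the general scale of blood counts. The exact multiples depend on the reference ranges and blood volume assumed above, but the conclusion does not change across those ranges. Endpoints, sample size, error rates and analyses are untouched. How far the slip reached trial conduct is unknown: the article shows neither the operational documents nor any wrongly enrolled patient.

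**What to change.** 1. Compare the unit of both limits in the published Table 2 with the full protocol and the eligibility form, and correct it wherever it is wrong. State it in a unit that site laboratories report. This review proposes no threshold; the sponsor has to reconcile the documents.
2. Only if the full protocol or the eligibility form carries the same per-litre unit, list the screening platelet and neutrophil counts of the patients already randomised against the reconciled limits, and report any who fall below them as eligibility deviations.

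Step 1 costs a document check and a correction of one unit in two entries. Step 2, if it is needed, costs one listing from screening results, which should already be on file.

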#### Interventions

Intervention drugs administered in each stage

**Phase II, first stage -** six arms with six different interventions will be designed:

ATV.DCV.SOF/DCV.PbO ATV.PbO DCV.PbO SOF/DCV.

**Phase II, second stage -** four arms with four different interventions will be designed:

Best of the first stage.Best of the first stage + the second best.PbO best first stage.PbO best first stage + PbO second best.

**Phase III, third stage -** two arms with two different interventions will be designed:

Best antiviral alone or in combination (defined in Stage 1 or 2).PbO best antiviral alone or in combination.

The doses and administration routes of the study drugs are described in table 3. If swallowing is impossible for any reason, the protocol provides for the use of the study drugs via a nasogastric or nasoenteral tube. The study drugs will be donated by pharmaceutical companies, with ATV (and PbO) donated by Fundação Oswaldo Cruz (Fiocruz) and DCV, SOF and respective PbOs donated by Blanver Farmoquímica e Farmacêutica.

**Table 3 t3:** Study drug dosage

Drug	Pharmaceutical form	Route of administration/ instructions for use	Frequency of administration	Conservation
Daclatasvir/placebo DCV	Coated tablets/ 28 tablets bottles*	Orally with or without food	2 tablets once daily on D1, 1 tablet once daily from D2 to D10	Room temperature 15 to 30°C
Sofosbuvir/placebo SOF	Coated tablets/ 28 tablets bottles*	Orally with or without food	1 tablet twice daily on D1, 1 tablet once daily from D2 to d10	Room temperature 15 to 30°C
Atazanavir/placebo ATV	Capsules with packs of 30 capsules*	Orally with food	2 capsules twice daily on D1, 1 capsule twice daily from D2 to d10	Room temperature 15 to 30°C

DCV - daclatasvir; SOF - sofosbuvir; ATV - atazanavir; D - day.

* Coated tablets for daclatasvir and sofosbuvir treatments and placebos and capsules for atazanavir treatment and placebo are identical in physical appearance.

#### Discontinuation of the drug treatment and safety criteria

The set of primary analyses for safety and efficacy will include individuals who received at least one dose of the study drug. Emerging treatment data will be analyzed and defined as data collected from the administration of the first study drug dose to the date of administration of the last study drug dose plus 30 days.

At medical discretion, the study drug(s) will be discontinued if a research participant meets one of the following criteria:

The researcher considers that the discontinuation of the study drug is in the best interest of the research participant.Elevated levels of alanine aminotransferase (ALT) or aspartate aminotransferase (AST) greater than ten times the value of the upper limit of normal (ULN). Elevations in ALT or AST levels often follow the clinical course of COVID-19, whether they are due to shock, sepsis or even direct SARS-CoV-2 infection in liver cells.^(10)^ These changes may occur in the two study groups: active drug or PbO.Elevated levels of ALT or AST greater than 3x the ULN **WITHOUT** an increase in alkaline phosphatase levels confirmed in a new test performed within 48 hours **AND** the presence of one of the following conditions:Total bilirubin level > 2 times the ULN.International Normalized Ratio (INR) > 2.Elevated ALT or AST levels greater than 3x the ULN accompanied by the presence of the following two conditions:Onset or worsening of fatigue, nausea, vomiting, discomfort in the upper abdomen, or fever.Rash and/or peripheral eosinophilia (> 5%).Any Grade 3 or greater rash accompanied by symptoms.Any Grade 4 AE or laboratory abnormality considered related to the study drug.

#### Discontinuation of one arm of the study for safety

The criteria for discontinuing one arm of the study for safety are the occurrence of one of the following 3 conditions:

Presence of the components of Hy’s Law^(11)^* which consists of the presence of all of the following conditions confirmed by an adjudicating committee of 2 independent evaluators:The study drug causes a higher incidence of hepatocellular injury confirmed by a > three times ULN increase in ALT and AST levels than the PbO group.Increase in ALT or AST levels > three times ULN and elevation of total bilirubin levels > two times ULN without signs of cholestasis (elevated alkaline phosphatase levels).No other explanation for the combination of the changes described above, such as the presence of hepatitis A, B, C, use of vasopressors or IMV; acute or preexisting hepatic disease or the presence of another drug capable of causing the observed injury.Elevated ALT and AST levels > five, ten or twenty times ULN more frequently in the treated group than in the control group after 48-hour reassessments.Presence of more serious adverse events (SAEs) defined in Section S.5 (Supplementary material 1) in the treatment arm than in the PbO arm.

Patients with COVID-19 may progress to sepsisassociated liver injury, which makes characterizing all the Hy Law criteria in these patients very challenging. For this study, we will consider a modified definition of Hy’s Law that will be present when the 3 criteria described above are met in the absence of shock or severe acute respiratory failure with the need for mechanical ventilation.

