### Sample size

We intend to include 252 patients in Phase II/Stage 1 (189 in the active groups and 63 in the PbO group) and 189 patients in Phase II/Stage 2 (126 in the active groups and 63 in the PbO group). For Phase III, 564 additional participants will be randomized (376 in the active group and 188 in the PbO group). Thus, at the end of Phase III, 314 patients will have been evaluated in the PbO group and between 439 and 502 patients will have been evaluated in the treatment group if the study persists through the three phases. More details about the sample size calculation are described in Supplementary material 2 (Statistical Analysis Plan).

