### Statistical methods

The main analysis of the data from this study will be performed on patients of the intention-to-treat (ITT) population. The definition of the analysis populations and more details on statistical methods are available in the Statistical Analysis Plan. The analyses will be performed with R software (R Core Team, 2020).

All the different PbOs for ATV, DCV and SOF will always be analyzed together as a single PbO group.

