### Analysis of primary outcomes

#### Phase II/1

In Phase II/1, patients will be allocated in ratio of 3:3:3:1:1:1 (3 for each treatment group and 1 for PbO). For Phase II/1, the parameter of interest for the decision will be the comparison of the decay rates of the viral load logarithm from real time polymerase chain reaction (RTPCR) to COVID-19 in 9 days between the treatment groups compared with the control using a mixed linear model.

The interim analysis, which is planned to begin when 126 patients are randomized and followed for at least 10 days, will be exclusively conducted for a patient safety assessment (based on safety outcomes and adverse events).

At the end of Phase II/1, each group will be compared with the PbO group considering a significance level for each comparison of 0.067 (Bonferroni correction for multiple comparisons), such that the global type I error of Phase II/1 will be 0.20. If no treatment is significantly different from the PbO group at the stipulated level of significance, the study will be terminated at this stage.

Among the treatments significantly different from the PbO group in relation to the linear rate of viral load decay, the one with the highest rate of decay and considered safe by the independent study safety committee will be a candidate treatment for inclusion in Phase II/2 of the study. It will be combined with the drug responsible for the second highest linear decay rate to comprise the second Phase II/2 treatment group.

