#### Phase III

The third stage of the study will proceed in a 2:1 allocation (two active treatments for each PbO), with a minimum inclusion of 189 patients and a maximum of 564. The study will perform interim analyses that may interrupt the study due to safety, futility, or efficacy, using all participants already randomized in Phases II/1 and II/2, since the primary efficacy outcome of Phase III (time of use of ventilatory support within 15 days) will be analyzed for all patients from these earlier phases as well.

The hypothesis test for the treatment effect will be performed using a generalized additive model of location and scale considering the distribution of a beta-binomial mixture with inflated zeros for the data adjusted by age and considering the random effect of the center for each intercept (model for the beta-binomial part and for the probability of zeros).

Phase III has three interim analyses planned, m = 3, for each third of the collected sample. The interim analyses consider stop limits according to the O’Brien-Fleming criterion, with significance levels of 0.06%, 1.51% and 4.71%, respectively, to maintain the global significance level at 5%. In Phase III, discontinuations due to futility will be allowed and use the same stopping criteria defined for efficacy.

Although the PbO group is composed of individuals receiving PbOs for three separate drugs (sometimes in combination), it will always be evaluated as a single group after gathering information from all “PbO arms”.

Secondary/exploratory outcomes and additional analyses are described in Supplementary material 1 (Section S4.1).

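### The arm-level safety criterion on serious adverse events is a bare inequality: applied literally, an equally safe arm meets it 42–46% of the time in Phase II/1 (assumed risk 5–30%)

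*Protocol article*

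**What the plan says.** In the protocol article, the section *Discontinuation of one arm of the study for safety* opens with "The criteria for discontinuing one arm of the study for safety are the occurrence of one of the following 3 conditions". One condition is therefore enough.

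- **Condition 1** is a modified Hy's Law definition, which two independent evaluators must confirm.
- **Condition 2** concerns ALT and AST elevations that occur "more frequently in the treated group than in the control group after 48-hour reassessments".
- **Condition 3** is "Presence of more serious adverse events (SAEs) defined in Section S.5 (Supplementary material 1) in the treatment arm than in the PbO arm".

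Conditions 2 and 3 carry no margin, test, confidence limit or minimum number of events.

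The comparator is settled elsewhere. *Statistical methods* says "All the different PbOs for ATV, DCV and SOF will always be analyzed together as a single PbO group".

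Safety is also treated as a matter of judgement in three places. *Rules for changing the study stage* requires drugs to be both effective and safe, and for the daclatasvir route it refers to the DSMB's interpretation. *Phase II/1* requires the advancing treatment to be considered safe by the independent committee. *Trial organization and oversight* gives the DSMB the interim analyses and an advisory role toward the Steering Committee.

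**The concern.** When two groups have the same true risk, one of them will show more events than the other simply by chance, and unless they tie it is the active arm about half the time. A criterion that asks only which group has more therefore cannot separate a harmful arm from a harmless one. More patients do not cure this. On proportions the chance of a flag stays close to one half, and on raw counts under unequal allocation it moves toward certainty.

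Being safe is a condition for every stage change, and the study ends if no drug is both effective and safe. If condition 3 were applied as written, the choice of treatment for Phase II/2 and Phase III would depend partly on chance. If the DSMB instead sets it aside, the article does not say on what basis an SAE imbalance is to be read.

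**Working it through.** **Inputs**

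- Phase II/1 sizes (*Sample size*): "We intend to include 252 patients in Phase II/Stage 1 (189 in the active groups and 63 in the PbO group").
- Phase II/1 allocation (*Phase II/1*): "In Phase II/1, patients will be allocated in ratio of 3:3:3:1:1:1 (3 for each treatment group and 1 for PbO").
- Half-way safety look (*Phase II/1*): "planned to begin when 126 patients are randomized and followed for at least 10 days".
- Phase III: "The third stage of the study will proceed in a 2:1 allocation", with 376 active and 188 placebo (*Sample size*).
- SAE risk: not given in the article. Assumption: 5–30% of patients, the same in both groups, with 1% and 2% shown as lower cases.

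**Reproducing the article's own sizes.** Blocks have 12 positions. Each active arm gets 252 × 3/12 = 63, and the three placebos together get 252 × 3/12 = 63. In Phase III, 564 × 4/6 = 376 and 564 × 2/6 = 188. All agree with the article. Against pooled placebo, Phase II/1 is a 63 v 63 comparison, so counts and proportions give the same answer there.

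**One arm, one look, equal risk.** Let X_T and X_P be independent Binomial(63, p). By symmetry, P(X_T > X_P) = [1 − P(X_T = X_P)] / 2. At p = 10% the tie probability is 0.119, so the result is (1 − 0.119)/2 = 0.44.

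| True SAE risk, both groups | P(arm meets condition 3), 63 v 63 |
|---|---|
| 1% | 0.30 |
| 2% | 0.37 |
| 5% | 0.42 |
| 10% | 0.44 |
| 20% | 0.46 |
| 30% | 0.46 |

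The shortfall from one half is ties, which are commoner when events are rare.

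**At least one of three equally safe arms.** The arms share one placebo group, so P = 1 − Σ_k P(X_P = k) · P(X_T ≤ k)³. This gives 0.67 at 5%, 0.69 at 10%, 0.71 at 20% and 0.71 at 30%.

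**Adding the half-way look.** 126 patients give about 31 or 32 per group. Simulating 400,000 trials, with the condition checked at about half and at full enrolment, one arm meets it at either look in 52–58% of trials (risk 5–30%), and at least one of three does in 78–82%.

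**An arm that truly lowers risk.** With 15% on active and 20% on placebo, 63 v 63, P(X_T > X_P) = 0.19.

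**Phase III, 376 v 188, equal risk.** Here the basis of comparison matters.

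| True SAE risk | Proportions | Raw counts |
|---|---|---|
| 5% | 0.48 | 0.96 |
| 10% | 0.485 | 0.995 |
| 20% | 0.49 | about 1 |

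If patients from the earlier stages were added (439 v 314, using the smaller active total in *Sample size*), the count figures would be 0.83 at 5% and 0.93 at 10%, with proportions still about one half.

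No rate was computed for condition 2. It has the same form, but the article gives nothing on how often such elevations occur.

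**The case against.** The strongest reply is that no arm is dropped mechanically. The stage-change rules, the Phase II/1 analysis section and the oversight section all bring in committee judgement, and *Current status* mentions a DSMB Charter that is not shown and may hold operating boundaries. This stands to the extent that a reader might infer that equally safe arms will in fact be discarded about half the time. The documents support only that such arms meet the criterion that often. It does not remove the point, because the section states its conditions as the criteria for discontinuing an arm without calling them advisory. The patient-level rule just before it does begin by invoking medical discretion.

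Other stronger readings also fail:

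- A reader might compare each arm with its own placebo (63 v 21) because condition 3 speaks of a single placebo arm. The pooling statement excludes that.
- A reader might take condition 3 to be a count. The wording does not say so, and Table 1 expresses the SAE outcome as a percentage. The near-certain Phase III flag holds on the count reading only.
- A reader might conclude that no arm-stopping criterion is left if the DSMB disregards condition 3. Hy's Law remains, and so do the Phase III interim analyses that may stop for safety.

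The supplementary section that defines the qualifying SAEs is not shown. A narrow definition would lower the event risk, and with it the flag probability (30% at 1% risk), but it would not change the inequality.

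**Conclusion.** The point holds as a badly fixed rule, not as missing detail. Against pooled placebo in Phase II/1, an equally safe arm meets condition 3 with probability 42–46% at one look. At least one of three does so in 67–71% of trials (about 78–82% over two looks), and an arm that truly lowers risk from 20% to 15% still does in 19%. In Phase III the figure is 48–49% on proportions and at least 96% on counts, and the section does not say which applies.

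These results assume literal application and a 5–30% SAE risk that the article does not state. At 1–2% risk the single-arm Phase II/1 figure falls to 30–37%. The size applies to condition 3; condition 2 shares only the form. How often an arm would really be discontinued depends on DSMB practice, which cannot be judged from what is shown.

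**What to change.** Reconcile the arm-discontinuation section with the sections that give safety to DSMB judgement, in four steps:

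1. State that conditions 2 and 3 are guidelines to the DSMB.
2. Define the comparison as the proportion of patients with at least one qualifying event, each active arm against the pooled placebo group, in every stage.
3. Report the excess with its statistical uncertainty (a confidence interval or a posterior probability of excess), and state how often an equally safe arm would be flagged, counting all planned looks.
4. Leave the clinical threshold and the decision to the DSMB.

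The cost is wording in the protocol and the DSMB Charter; no new data are needed. The downside is that a small true excess would be flagged later than under a rule that reacts to any excess. *Current status* reports 256 patients already randomized against 252 planned for Phase II/1, so the change would mainly affect the Phase II/1 stage decision and the later stages.
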